**Visit procedures at visit (Visit 2, day 7 ± 2 days )**

- Date of visit
- Physical examination / Vital signs
- Concomitant medications
- Bodyplethysmography
- Bronchodilator response to Salbutamol
- Completing Questionnaires (CAT)
- Inhalation of blinded medication by nebuliser
- Sputum collection
- Recording side effects
- Recording “ease of expectoration”.
- Lung function monitoring up to one hour after sputum collection
- Drug dispensation
- Recording of Adverse Events
- Appointment for the next visit

**Visit procedures after end of treatment phase A at visit (Visit 3, day 21 ± 4 days)**

- Date of visit
- Physical examination / Vital signs
- Concomitant medications
- Bodyplethysmography
- Bronchodilator response to Salbutamol
- Completing Questionnaires (CAT and TDI, and St. George)
- Inhalation of blinded medication by nebuliser
- Sputum collection
- Recording side effects

- Recording “ease of expectoration”.
- Lung function monitoring up to one hour after sputum collection
- Appointment for the next visit after “Wash-out –phase”.

**Visit procedures after washout (+ 7-14 days) before treatment phase B at visit 4**

- Date of visit
- Physical examination / Vital signs
- Concomitant medications
- Bodyplethysmography
- Bronchodilator response to Salbutamol
- Completing Questionnaires (CAT, BDI and St. George)
- Drug dispensation
- Inhalation of blinded medication by nebuliser
- Sputum collection
- Recording side effects
- Recording “ease of expectoration”.
- Lung function monitoring up to one hour after sputum collection
- Appointment for the next visit

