| CONDITION                            | Mucolytic treatment in chronic bronchitis                                                                                                                                                                                                                                                                                                                                                                                                                                                                                                                                             |
| OBJECTIVE(S)                         | To evaluate the mucolytic activity of Tylaxopol compared to saline (0.9%) in chronic bronchitis patients. Lung function parameters, biomarker profiles in sputum and serum, and clinical symptoms by standardized questionnaires [COPD activity index (CAT), Baseline Dyspnea Index (BDI) & Transition Dyspnea Index (TDI)] will be evaluated in response to Tylaxopol vs. saline in chronic bronchitis patients.                                                                                                                                                                     |
| INTERVENTION (S)                     | Chronic bronchitis patients (will be randomly assigned to either inhaled Tacholiquin® 1% 5ml or saline solution each three times daily for 3 weeks. After one week of washout Tylaxopol treated patients will receive saline solution and vice versa for another 3 weeks.                                                                                                                                                                                                                                                                                                             |
| KEY INCLUSION AND EXCLUSION CRITERIA | Key inclusion criteria: Patients aged between 40 and 85 years suffering from chronic bronchitis (COPD). Key exclusion criteria: Patients with other underlying chronic diseases.                                                                                                                                                                                                                                                                                                                                                                                        |

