| OUTCOME(S)                           | The primary outcome variable is sputum weight after treatment as difference between that after Tylaxopol and after saline. Key secondary endpoint(s) are: symptom scores (CAT, BDI and TDI), ease of sputum production by analog scale, changes in lung function parameter (FVC, FEV1, MEF25, RV, RV/TLC), LCI, sputum parameters and biomarker profiles (IL-1, IL-6, IL-8), in sputum and response to Tylaxopol vs. saline. Assessment of safety: Safety will be ensured by monitoring of symptom scores and rescue medication, lung function FEV1 and adverse events. |
| DURATION OF TREATMENT AND FOLLOW-UP  | Duration of treatment per treatment arms (3 weeks): Each patient will be treated in a cross-over double-blinded randomized design either with Tylaxopol and or saline. During each treatment arm is a one week washout phase.                                                                                                                                                                                                                                                                                                                                                  |
| STUDY TYPE                           | This study is a monocenter double-blind, placebo-controlled (DBPC) crossover randomised trial.                                                                                                                                                                                                                                                                                                                                                                                                                                                                                        |

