### Study Flow Chart and Procedures

| Period                                        | I                                  | II                | III               | IV                         | V                 | VI                 |
|-----------------------------------------------|------------------------------------|-------------------|-------------------|----------------------------|-------------------|--------------------|
|                                               | Treatment Phase A                  | Treatment Phase A | Treatment Phase A | Treatment Phase B          | Treatment Phase B | Treatment Phase B  |
| Visit(s)                                      | 1                                  | 2                 | 3                 | 4                          | 5                 | 6                  |
|                                               | Recruitment - Start of Treatment A | Treatment Visit   | End of Phase I    | Start of Treatment Phase B | Treatment Visit   | End of Phase B     |
| Weeks (W)                                     | 0                                  | 1                 | 3                 | 4                          | 6                 | 7                  |
| Day                                           | 0                                  | 7 ±2              | 21±4              | 28±14                      | 7±2 after Visit 4 | 21±4 after Visit 4 |
| Written Informed consent                      | X                                  |                   |                   |                            |                   |                    |
| Demographic data                              | X                                  |                   |                   |                            |                   |                    |
| Medical/COPD history and concomitant diseases | X                                  |                   |                   |                            |                   |                    |
| Smoking History/Status                        | X                                  |                   |                   |                            |                   |                    |
| Concomitant medications                       | X                                  | X                 | X                 | X                          | X                 | X                  |

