## 5.6. **TREATMENT ASSIGNMENT**

At Visit 1 (Day 0) eligible patients will be assigned a randomization number in consecutive, ascending order.

In order to ensure random allocation, each new consecutive patient randomized is to be given the box bearing the lowest available randomisation number.

The investigator must maintain an accurate record of the shipment and dispensing of study drug in a drug accountability log. An accurate record of the date and amount of study drug dispensed to each patient and returned must be available for inspection at any time.

The investigator will be asked to return all unused medication at the end of the study.

Volunteers are required to be dosed so that the time window between visits is within 7 days of the scheduled administration dates.

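### The flow chart's window for Visit 4 (day 28±14, not tied to Visit 3) permits a shorter washout than the protocol intends

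*Protocol*

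**What the plan says.** The protocol describes the interval between the two treatment phases in three places.

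- **Synopsis.** The intervention row says: "After one week of washout Tylaxopol treated patients will receive saline solution and vice versa for another 3 weeks". The duration row says: "During each treatment arm is a one week washout phase". Both give one week.
- **Section 6.2.1.** The heading for Visit 4 reads: "Visit procedures after washout (+ 7-14 days) before treatment phase B at visit 4". The Visit 3 list, headed "Visit procedures after end of treatment phase A at visit (Visit 3, day 21 ± 4 days", includes a dose on site ("Inhalation of blinded medication by nebuliser") and ends with "Appointment for the next visit after “Wash-out –phase".
- **Flow chart.** The day row gives 21±4 for Visit 3 and 28±14 for Visit 4, and names no reference visit for Visit 4. The next two entries in that row are relative: "7±2 after Visit 4 | 21±4 after Visit 4". The weeks row gives week 3 for Visit 3 and week 4 for Visit 4.

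**The concern.** In a crossover trial the washout separates the two treatments, and its length should be the same rule wherever a site looks it up. Here the flow chart, a table that sites commonly schedule from, gives the visit that ends the washout a tolerance of two weeks either way. It counts that visit from day 0 rather than from the last phase A dose. The chart anchors Visits 5 and 6 to an earlier visit, so the same device was available for Visit 4.

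At stake are the data collected at Visit 4. Section 9.4 includes Day 1 data in the secondary analyses and treats the acute Day 1 sputum weight in each treatment arm with the method used for the primary parameter. Day 1 of phase B is Visit 4. If some patients arrive there a few days after their last phase A inhalation and others after three weeks, any residual effect of phase A would enter those data unevenly.

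**Working it through.** **Inputs**
- Visit 3: day 21±4, so days 17 to 25 (flow chart and section 6.2.1).
- Phase A dosing: 21 consecutive days (section 5.3).
- Visit 4: day 28±14, so 28 − 14 = day 14 to 28 + 14 = day 42 (flow chart).
- Washout: one week (synopsis); 7 to 14 days (section 6.2.1).
- Visit 6: 21±4 days after Visit 4 (flow chart and section 6.2.1).

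Washout = day of Visit 4 − day of Visit 3. Visit 3 is taken as the day of the last phase A dose, because study drug is inhaled there.

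**Step 1: the nominal day.** 21 + 7 = 28. The centre of the flow-chart window agrees with a one-week washout and with the weeks row (week 4 − week 3 = 1 week).

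**Step 2: the tolerance.** With Visit 3 on day 21, the rule in section 6.2.1 gives 21 + 7 = day 28 to 21 + 14 = day 35. The flow chart gives days 14 to 42, which divide as follows:
- days 14 to 20: before phase A ends, so not usable as a start of phase B;
- days 21 to 27: washout of 0 to 6 days;
- days 28 to 35: washout of 7 to 14 days;
- days 36 to 42: washout of 15 to 21 days.

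The ±14 therefore follows neither from one week nor from 7 to 14 days. Among the days that can occur (21 to 42, which is 22 days), 7 are too short, 8 fit and 7 are too long. These counts describe what the chart permits. They do not say how often each gap would happen.

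**Step 3: does section 6.2.1 ever break the flow chart?**
- Earliest Visit 3: 17 + 7 = day 24 to 17 + 14 = day 31.
- Latest Visit 3: 25 + 7 = day 32 to 25 + 14 = day 39.

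Over all allowed Visit 3 dates, section 6.2.1 puts Visit 4 on days 24 to 39, wholly inside days 14 to 42. A site that obeys section 6.2.1 also obeys the chart. The converse fails: a site can obey the chart's day row and break section 6.2.1.

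**Step 4: which data are reached.** Visit 6 falls 21 − 4 = 17 to 21 + 4 = 25 days after Visit 4, whenever Visit 4 takes place. The primary phase B sputum is therefore collected at least 17 days into phase B. What sits directly after the washout is the set of Visit 4 measurements. The protocol gives neither the duration nor the sign of any residual effect of tyloxapol or saline, so no bias can be calculated.

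**The case against.** The strongest reply is that all the rules can be met together. As step 3 shows, the 7-to-14-day rule lies inside the chart's window, and one week can be read as the nominal value of that range. The protocol text also ties Visit 4 to the end of phase A: the appointment is made at Visit 3 for after the washout, and the Visit 4 heading repeats the interval. On this view the chart is only a wide outer limit, and harm arises only at a site that reads the day row and ignores the visit instructions. This stands, and it limits the point to a badly set flow-chart window. It does not remove the point, because days 14 to 20 cannot be right on any reading and days 21 to 27 undercut the stated washout.

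A reader might infer more in four ways, and the protocol does not support any of them.

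- **That no calendar day could satisfy the washout for every patient.** Days 24 to 31 and days 32 to 39 do not overlap, but nothing in the protocol asks for Visit 4 on one fixed day regardless of Visit 3.
- **That only 8 of 29 permitted days comply.** The 29 include days before phase A ends, which cannot occur as a start of phase B.
- **That section 5.6 shortens the washout further.** Its wording, "the time window between visits is within 7 days of the scheduled administration dates", is ambiguous. A reading of ±7 days around day 28 is conjecture, and it would also narrow the ±14 window.
- **That the blind review would have no rule for a short washout.** Section 6.2.1 supplies one, section 9.2 sends problem cases to that review, and detailed classification may be left to the statistical analysis plan.

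**Conclusion.** The point holds as an error in the flow chart. Its window for Visit 4 permits a washout of 0 to 21 days when Visit 3 is on day 21, against one week in the synopsis and 7 to 14 days in section 6.2.1. It also lists days before phase A has ended. A site working from the day row could start phase B after 0 to 6 days and still comply with that row.

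The data exposed are the secondary data of phase B Day 1, including acute sputum weight. A reader might go further and infer carryover into the primary comparison. The protocol does not support that: the phase B primary measurement comes 17 to 25 days after Visit 4, and no residual effect is described from which a size or direction could be derived.

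The conclusion assumes that day 28±14 is counted from day 0, as the layout of the day row indicates, and that the Visit 3 inhalation is the last phase A dose. It should be corrected, but it does not put the primary analysis in doubt.

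**What to change.** In the flow chart, replace 28±14 for Visit 4 with 7 to 14 days after Visit 3 (last phase A dose), in the same relative form already used for Visits 5 and 6. State the same 7-to-14-day washout in both synopsis rows and in section 6.2.1, so that every place gives one rule.

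This is a change of text only, with no added visits, patients or measurements. The downside is slightly tighter scheduling of Visit 4.

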**Visit procedures at visit 5 (day 7 ± 2 days after Visit 4)**

- Date of visit
- Physical examination / Vital signs
- Concomitant medications
- Bodyplethysmography
- Bronchodilator response to Salbutamol
- Completing Questionnaires (CAT)
- Inhalation of blinded medication by nebuliser
- Sputum collection
- Recording side effects
- Recording “ease of expectoration”.
- Lung function monitoring up to one hour
- Drug dispensation
- Recording of Adverse Events
- Appointment for the next visit

**Visit procedures at visit 6 end of treatment phase B (21 ± 4 days after Visit 4)**

- Date of visit
- Physical examination / Vital signs
- Concomitant medications
- Bodyplethysmography
- Bronchodilator response to Salbutamol
- Lung clearance index
- Completing Questionnaires (CAT, TDI and St. George)
- Drug dispensation
- Inhalation of blinded medication by nebuliser
- Sputum collection
- Recording side effects
- Recording “ease of expectoration”.
- Lung function monitoring up to one hour after sputum collection

Additional visits can be scheduled and performed according to the investigators judgment of how to best manage the patient. At these visits in addition to recording any SAEs, AEs and concomitant medication use, a physical examination, vital sign assessment and lung function tests will be performed.

Any unscheduled visits, follow-up visits and adverse events, are to be recorded in the other clinical visits CRFs.

**6.2.2. INSTRUCTIONS****MEDICAL HISTORY**

At Visit 1, medical history, and concomitant medication according to the CRF is obtained.

**PHYSICAL EXAMINATION AND VITAL SIGNS**

A physical examination is performed by the investigator at each visit.

The physical examination should include the following:

- General appearance
- Skin
- O2 Saturation
- Head
- Respiratory (lungs)
- Cardiovascular
- RR, pulse
- Musculoskeletal

## LABORATORY EXAMINATIONS

A venous blood is obtained at the following visits (Visit 1). An urine sample is analyzed by “Chek-stix Combo” at visit 1.

### Macrophage activation test (MAT)

The anti-inflammatory effect of Tyloxapol was measured by cytokine release after LPS-stimulation of whole blood cells. Briefly, EDTA-blood samples were diluted 1:10 with RPMI 1640 medium and stimulated with 5 ng/ml LPS from *E. coli* 026:B6 (Sigma-Aldrich Pharmaceuticals, Germany) in the presence of 0, 0.001, 0.01, 0.1 and 1.0 mg/ml Tyloxapol [22]. After a 24-hr incubation period at 37°C and 5% CO2, supernatants were harvested and stored at -80°C until further use.

Venous blood is sent to the laboratory of [name].

## URINE PREGNANCY TESTS

Pregnancy tests are obtained from all female volunteers of child-bearing potential. At Visit 1, a urine pregnancy test is obtained.

## PULMONARY FUNCTION-SPIROMETRY

Pulmonary function tests will be recorded whilst the subject is in a sitting position at every visits. Bodyplethysmography will be performed according to the European Respiratory Standards (ERS).

---

The following variables will be documented: FVC [L, % pred], FEV1 [L, % pred], MEF25 [L, % pred], FEV1/FVC (Tiffenau-Index), RV and RV/TLC.

In order to reduce variability, all measurements should be made at approximately the same time of day at each visit and on the same calibrated bodyplethysmography..

The FVC, FEV1, MEF 25%, FEV1/FVC, RV and RV/TLC recorded in the CRF must be taken from the maneuver obtained from the single “best test” curve and must be recorded as absolute values. The “best test” curve is defined as the spirogram that gives the largest FEV1.

Between treatment differences for FEV1, FVC and MEF 25% RV and RV/TLC will be analyzed at each visit using an analysis of covariance with pooled center, baseline, sex Least square mean differences based on the model will be calculated and 95% confidence intervals will be constructed.

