### **3 STUDY DESIGN**

The study will be a monocentre, randomized, double-blind, crossover, placebo-controlled study in 24 COPD patients (including 4 Drop-out) in order to achieve 20 evaluable patients for the statistical analysis. 'Evaluable' mean eligible COPD patients having met all the inclusion and none of the exclusion criteria, having performed all scheduled clinical visits and with a "good" compliance as defined in section 7.5.

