#### **9.4. ANALYSIS OF EFFICACY CRITERIA**

The primary endpoint is sputum weight after 3 weeks of Tylaxopol– that after 3 weeks of saline treatment which will be analyzed for the Per Protocol Population. Estimated differences will be presented together with 95% confidence intervals (CIs) for the difference and two-sided p-values from a corresponding t-test. This analysis will be repeated for the ITT Population.

Secondary endpoints: The analysis of symptom scores ((CAT, BDI and TDI), ease of sputum production by analog scale, lung function parameter (FVC, FEV1, MEF25, RV, RV/TLC), will use the same methodology as that for the primary endpoint, using the ITT population. The analysis will include Day 1 and week 3 data. In addition acute changes of sputum weight on Day 1 at each treatment arm will be analyzed as described for the primary parameter. Secondary analyses aim to determine the efficacy BP versus placebo to modulate CRP and reducing the symptoms.

Data will be summarized with respect to demographic and baseline characteristics, efficacy observations and measurements, and safety observations and measurements.

Primary and secondary confirmatory analyses will be performed and reported at the end of the double-blind treatment period. A full statistical analysis plan will be produced prior to unblinding the study.

Biomarker profiles (sputum cells, IL-1, IL-6, IL-8), in sputum will be analyzed using an analysis of covariance (ANCOVA) model with covariates of baseline, smoking status and treatment. Estimated treatment differences along with corresponding 95 % CIs will be presented for the treatment comparison.

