#### **9.5. EXPLORATORY ANALYSIS OF EFFICACY CRITERIA**

All statistical tests will be two-sided using  $\alpha=0.05$ . An appropriate pooled center algorithm will be defined prior to unblinding the data. No adjustment for multiple testing will be done since the primary variable and the primary population is well defined.

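### The protocol states two incompatible analyses for the same five lung-function variables, and the one in 6.2.2 lists no patient or period term and uses a centre factor in a single-centre trial

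*Protocol*

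**What the plan says.** Section 9.4 of the protocol covers the secondary endpoints. It says of lung function: "lung function parameter (FVC, FEV1, MEF25, RV, RV/TLC), will use the same methodology as that for the primary endpoint, using the ITT population". The primary endpoint's method is the difference between sputum weight after tyloxapol and after saline, with a 95% confidence interval and "two-sided p-values from a corresponding t-test". On time points, 9.4 adds: "The analysis will include Day 1 and week 3 data". The synopsis, 2.3 and 7.1.2 say the same in substance.

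Section 6.2.2, under Pulmonary function-spirometry, gives another analysis for the same five variables. It says that treatment differences "will be analyzed at each visit using an analysis of covariance with pooled center, baseline, sex", and that they are reported as least-squares mean differences with 95% confidence intervals. No patient, period or sequence term is listed, and no analysis population is named.

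On centres, section 3 says: "The study will be a monocentre, randomized, double-blind, crossover, placebo-controlled study". The synopsis also describes a single-centre trial. Section 9.5 nevertheless announces: "An appropriate pooled center algorithm will be defined prior to unblinding the data".

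**The concern.** These are two different analyses of one set of endpoints, and nothing in the protocol makes one of them main and the other supportive. A statistical analysis plan that follows either section departs from the other, so this is a conflict in what is already fixed and not a detail left for later.

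The version in 6.2.2 also does not fit the design. Under 5.3 each patient takes one product in phase A and the other in phase B, so at any single visit about half the patients are on each product. A treatment comparison made visit by visit therefore compares different people and makes no use of the patient as his or her own control, which is the reason for a crossover.

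Lung function is a key secondary endpoint, and the synopsis also names FEV1 among the safety measures. The number of comparisons differs as well: five variables at two time points give 10, and five variables at six visits give 30, with no multiplicity adjustment planned (9.5).

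**Working it through.** **1. The two plans side by side**

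| | Synopsis, 2.3, 7.1.2, 9.4 | 6.2.2 |
|---|---|---|
| Variables | FVC, FEV1, MEF25, RV, RV/TLC | the same five |
| Comparison | tyloxapol minus saline, t-test | ANCOVA, least-squares mean difference |
| Covariates | none stated | pooled centre, baseline, sex |
| Time points | Day 1 and week 3 | each visit (six visits) |
| Population | ITT | not stated |

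They agree only on the variables and on giving 95% intervals.

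**2. The plan's own figure.** No figure is stated for lung function. The only sizing is for sputum weight (9.3): difference 1.2 g, SD 1.7 g, N = 20, power 80%. With 1.7 g read as the SD of the within-patient difference, a paired t-test (noncentral t, two-sided alpha 0.05) has 80.6% power at n = 18 and 84.9% at n = 20. The stated size therefore holds, slightly on the safe side, and it rests on the paired comparison. The point made here leaves it unchanged.

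**3. Precision if 6.2.2 is followed literally.** Inputs: 20 patients (9.3), taken as 10 per sequence; common SD σ; correlation r between a patient's values in the two phases. The correlation between baseline and outcome is assumed to equal r. Degrees of freedom spent on covariates are ignored.

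- Paired, both phases: variance = 2(1 − r)σ²/20.
- ANCOVA at one visit, 10 v 10: variance = 2(1 − r²)σ²/10 = 4(1 − r²)σ²/20.
- Ratio = 4(1 − r²) / [2(1 − r)] = 2(1 + r).

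| r (assumed) | SE at one visit, in σ | SE paired, in σ | Variance ratio |
|---|---|---|---|
| 0.5 | √(4 × 0.75/20) = 0.387 | √(2 × 0.5/20) = 0.224 | 3.0 |
| 0.75 | √(4 × 0.4375/20) = 0.296 | √(2 × 0.25/20) = 0.158 | 3.5 |
| 0.9 | √(4 × 0.19/20) = 0.195 | √(2 × 0.1/20) = 0.100 | 3.8 |

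The protocol's correlation of 0.75 is for sputum weight. None is given for lung function, so 0.5 to 0.9 is an assumed range.

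**4. What happens if the phases are combined.** Call the sequence groups 1 and 2, with group 1 on tyloxapol in phase A. The phase A estimate is mean(1A) − mean(2A); the phase B estimate is mean(2B) − mean(1B). Their average is ½{[mean(1A) − mean(1B)] + [mean(2B) − mean(2A)]}, which is a mean of within-patient differences. Its variance is ¼ × 2 × 2(1 − r)σ²/10 = 2(1 − r)σ²/20, the paired value. The loss in step 3 therefore applies only while each phase stands alone.

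**5. Centre.** With one centre, the factor has a single level and coincides with the intercept. It cannot be estimated, and there is nothing to pool.

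**The case against.** The sentence in 6.2.2 is garbled: it runs into the next one, and treatment itself is missing from the list of terms. So the list may be incomplete, and each visit could mean matched visits of the two phases (1 and 4, 2 and 5, 3 and 6). This stands as a caution: the between-patient reading is the literal one, but not the only one. It does not remove the conflict. On the matched reading the listed model still has no patient term, so two measurements from one patient would be treated as independent.

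The within-patient method is also stated four times, once in the statistics section, while the ANCOVA appears once, among measurement instructions. Section 9.4 promises a full analysis plan before unblinding, and 9.2 provides a blinded review of the plan. This weakens any inference that a result could be chosen after the data are seen, because the protocol provides for settling the method blind. It does not say which text prevails.

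Three stronger readings are tempting and are not supported:

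- A variance ratio of 3.5 might be taken to mean that about 70% of the patients are thrown away (1 − 1/3.5 = 0.71). That holds only for one phase analysed alone at an assumed correlation. Section 6.2.2 does not describe combining the phases, but does not exclude it, and step 4 shows that averaging them restores the paired precision.
- Sex might be listed as a fault. In a between-patient ANCOVA it is a legitimate covariate; it is redundant only in a within-patient comparison.
- The centre term might be thought to distort results. A one-level factor drops out and changes no estimate, interval or p-value.

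**Conclusion.** The contradiction is real. One set of five variables has two stated analyses that differ in model, covariates and time points, with no order of precedence. Taken literally, the 6.2.2 version is a between-patient comparison of about 10 v 10 at each visit. If the phases are not combined, its variance is 3.0 to 3.8 times that of the paired comparison. That range rests on 20 patients split evenly, an assumed r of 0.5 to 0.9, and a baseline correlation equal to r. Pooled centre is empty wording in both places.

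A reader might infer that the trial's main result is at risk. It is not: the primary endpoint and the sample size of 20 do not depend on 6.2.2. Nor should much be built on FEV1 as a safety measure, since the synopsis names it but 7.2 and 9.6 do not list it. The point concerns secondary endpoints and should be corrected before unblinding.

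**What to change.** Delete the ANCOVA sentence in 6.2.2 and the pooled-centre sentence in 9.5. State one within-patient crossover analysis of lung function, the same as for the primary endpoint: tyloxapol minus saline, with 95% confidence interval and t-test, in the ITT population. A period term may be added. A full mixed model is not needed to cure the conflict and would be a third method that neither section contains.

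Fix the time points as Day 1 (Visit 1 against Visit 4, the first visit of each phase) and week 3 (Visit 3 against Visit 6), and use them in every section. If Visit 2 against Visit 5 is also compared, label it supportive.

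The cost is protocol wording only. No visit, measurement or patient number changes.
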